**a. Specific Aims**

**Specific Aim 1: To estimate the effect of receiving CBCT on empathic accuracy and resilience among chaplain residents providing spiritual care to hospitalized patients.**

We will conduct a naturalistic study of up to 30 chaplain residents serving the Spiritual Health department of Emory Healthcare, and who will receive CBCT during the first unit of their year-long residency (the early-start group) or approximately midway through the residency year (the delayed-start group). Empathic accuracy and resilience will be measured for all participants before the early-start group receives CBCT (baseline, or T0); after the early-start group completes CBCT (T1); before the delayed-start group receives CBCT (T2), and after the delayed-start group completes CBCT (T3). See **Figure 3** for study schematic. The change in mean score of empathic accuracy and resilience measures from T0 to T1 among participants in the early-start group will be compared to the change in mean score among participants in the delayed-start group over the same time period.

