**Audio Recordings:**

Chaplain residents will wear a recording device that will record chaplain-patient interactions. Patients will be informed that they can stop the recording at any time and that they can ask for their recording to be deleted at any time if they no longer wish for it to be a part of the study. Audio recordings will be de-identified, such that patient and chaplain are only linked with participant IDs and identity will not be available to anyone coding the recordings. Patients and chaplain participants will complete an assent form to indicate how their recordings can be used, including whether recordings can be used for other research projects by our team, by other researchers, and for scientific presentation of these data.

1. **Data analysis**

We will analyze the data to test the hypothesis that CBCT improves chaplain residents’ empathic accuracy and resilience in a hospital setting. SAS 9.4 and SPSS 23 will be used to conduct statistical analysis of the collected data. Descriptive statistics will be used to describe selected characteristics of participants by group, expressed as frequencies and percentages. The primary outcomes of empathic accuracy, compassion fatigue, compassion satisfaction, empathy, anxiety, and depressive mood will be measured as pre-to-post differences in the measurement scores, i.e., T1 – T0. For the early-start group and T3 – T2 for the delayed-start group. We will examine the effect of CBCT by analyzing the correlated, repeated-measure data (T1 – T0) – (T3 – T2) using mixed linear models, implemented in SAS Proc Mixed. Mean pre-to-post differences will be compared across groups.

To evaluate whether the effects of CBCT persist over time, differences between mean scores on measures of empathic accuracy and resilience for the early-care group will be compared across four time points: from baseline measurement to early-group post-CBCT measurement (T1 – T0), from early-group post-CBCT measurement to delayed-group pre-CBCT measurement (T2 – T1)_,_ and from delayed-group pre-CBCT measurement to delayed-group post-CBCT measurement (T3 - T2). To evaluate whether the effects of CBCT depend on the timing of program delivery, the differences between mean scores on empathic accuracy and resilience will be compared for each group during the period following receipt of the CBCT program; that is, (T1 – T0) – (T3 – T2).

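### The formula given for the CBCT effect sets one CBCT window against another, so it does not estimate the effect that Aim 1 defines

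*Protocol*

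**What the plan says.** **Schedule (Protocol, Specific Aim 1).** The first two assessments fall "before the early-start group receives CBCT (baseline, or T0); after the early-start group completes CBCT (T1"), and the last two "before the delayed-start group receives CBCT (T2), and after the delayed-start group completes CBCT (T3"). CBCT is therefore delivered between T0 and T1 in the early-start group and between T2 and T3 in the delayed-start group.

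**Aim 1.** The early-start change over T0–T1 "will be compared to the change in mean score among participants in the delayed-start group over the same time period". The comparator is the delayed-start group before it has had CBCT.

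**Data analysis.** The section opens with its purpose: "We will analyze the data to test the hypothesis that CBCT improves chaplain residents’ empathic accuracy and resilience in a hospital setting". It then defines the primary outcomes as pre-to-post differences, T1–T0 "For the early-start group and T3 – T2 for the delayed-start group", and continues: "We will examine the effect of CBCT by analyzing the correlated, repeated-measure data (T1 – T0) – (T3 – T2"). Mixed linear models are to be used, and the mean differences compared between groups.

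**Aim 3, same section.** For the timing question, differences in mean scores "will be compared for each group during the period following receipt of the CBCT program", and the expression given is again (T1–T0) – (T3–T2).

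The Data analysis section nowhere states the same-period comparison that Aim 1 describes.

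**The concern.** A test of whether CBCT improves outcomes needs a comparison with people who have not received it over the same stretch of the residency. The study has one: the delayed-start group from T0 to T1. The stated formula leaves that comparator out and uses the delayed-start group's own CBCT window instead. One number is then to be read both as the effect of CBCT and as the effect of its timing.

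The Synopsis says the pilot data will be used to estimate efficacy and inform a randomised trial. If CBCT worked about equally well in both groups, the stated analysis could give an estimate near zero and be read as showing no effect. If CBCT did nothing but residents' scores drifted differently early and late in the year, the drift could be read as an effect. The result also carries into Aim 5, because the mediation models take up only those chaplain variables found to be affected by CBCT.

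**Working it through.** The Protocol gives no power calculation, SD, effect size, alpha or allocation, so there is no figure of its own to reproduce. The main check is algebra and needs none of these.

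**Notation.** dE and dD are the CBCT effects in the early-start and delayed-start groups. p1 and p3 are the background changes over T0–T1 and T2–T3, taken as common to both groups.

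**Expected changes, from the schedule in Aim 1**
- Early-start, T1–T0: dE + p1
- Delayed-start, T1–T0: p1
- Delayed-start, T3–T2: dD + p3

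**Contrasts**
- Stated in Data analysis: (dE + p1) – (dD + p3) = (dE – dD) + (p1 – p3)
- Defined in Aim 1: (dE + p1) – p1 = dE

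The stated contrast is zero when dE = dD and p1 = p3. In no case does it isolate dE.

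**Illustration.** Assumptions: 15 per group (an even split of the stated maximum of 30), score SD 1, correlation 0.5 between assessments, so change SD = √(2 × (1 – 0.5)) = 1, two-sided alpha 0.05, t-test on change scores, 20,000 simulated trials per row. Effects and background changes are in SD units. Expectations come from the formulas above; rejection rates are simulated.

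| dE | dD | p1 | p3 | Stated contrast: expectation, rejects | Aim 1 contrast: expectation, rejects |
|---|---|---|---|---|---|
| 0 | 0 | 0 | 0 | 0, 5% | 0, 5% |
| 0.8 | 0.8 | 0 | 0 | 0, 5% | 0.8, 56% |
| 1.2 | 1.2 | 0 | 0 | 0, 5% | 1.2, 89% |
| 0.8 | 0.4 | 0 | 0 | 0.4, 18% | 0.8, 57% |
| 0.8 | 0.8 | –0.3 | 0 | –0.3, 13% | 0.8, 56% |
| 0 | 0 | –0.3 | 0 | –0.3, 12% | 0, 5% |

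The simulated mean contrasts agree with the formulas to within 0.01. Under the same assumptions, power for Aim 1's contrast from the noncentral t distribution is 26% at 0.5 SD, 56% at 0.8 and 75% at 1.0.

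Rows two and three show no response to a real effect that is equal in both groups. In row four the contrast returns the timing difference, 0.8 – 0.4 = 0.4. In row five CBCT works equally well in both groups, yet the contrast is negative. In row six CBCT does nothing, and the contrast reports the calendar difference.

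**The case against.** **A within-resident reading.** All residents have all four scores. One could form (T1–T0) – (T3–T2) within each resident and compare its mean between groups, as in a crossover. If the early-start effect persists, the expectations are dE + p1 – p3 and p1 – p3 – dD. Their difference is dE + dD, or 1.6 when both effects are 0.8 (1.59 in simulation). The reference to repeated-measure data and to comparison across groups lends this some support, and the sentence assigning windows to groups is broken in the text. That sentence nevertheless gives each group a single window, and the same expression is reused for timing, where the crossover form makes no sense. Even on this reading it would not be Aim 1's contrast.

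**Only a pilot, and a SAP may exist.** Both are fair points. But the Protocol does not leave the contrast open: it states a specific one that conflicts with its own aim. Estimation suffers as much as testing.

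**Stronger readings that the documents do not support**
- *The study cannot answer Aim 1.* It can: Aim 1 describes the right comparison in words, and every resident is measured at T0 and T1. The fault lies in the formula.
- *The contrast is zero whenever CBCT works equally well in both groups.* Background change must also be equal across the two windows.
- *Calling the data correlated is a mistake, because the two changes come from different people.* The phrase describes the data, and each resident's repeated scores are correlated. It does not claim a within-person contrast.

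**Conclusion.** The point holds as a contradiction inside the Protocol that must be corrected. The formula offered for the CBCT effect estimates (dE – dD) + (p1 – p3). That is not the effect, it departs from Aim 1, and it is the expression given for Aim 3. The conclusion rests only on the assessment schedule and on the window assigned to each group.

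The rejection rates are illustrative and depend on the assumed 15 per group and change SD of 1. The 5% rate further requires equal effects and equal background change. The power figures for Aim 1's contrast show the scale of what is lost; they do not establish the error.

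A reader might infer that Aim 1's contrast is free of assumptions. It is not: the study is described as naturalistic and no randomisation is mentioned, so the contrast equals dE only if both groups share the same background change over T0–T1. Nor is the formula a clean measure of timing under Aim 3, since p1 – p3 remains in it.

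**What to change.** In the Data analysis section:

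1. Define the Aim 1 outcome as T1–T0 in both groups.
2. State the test of the CBCT effect as (T1–T0) early-start minus (T1–T0) delayed-start, fitted as the group-by-time contrast over T0–T1 in the mixed model.
3. State that, with no randomisation described, this assumes the two groups share the same background change over T0–T1.
4. Keep (T1–T0) early-start minus (T3–T2) delayed-start for Aim 3 only.

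A T1 score adjusted for T0 should not be treated as an interchangeable substitute. In non-randomised groups it can estimate a different quantity, and Aim 1 specifies change in mean score.

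The cost is a change of wording. No new assessment or participant is needed, because all residents already complete T0 and T1.

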**Specific Aim 4: To evaluate whether CBCT-informed interventions improve patient outcomes.**

Upon completion of their training program, chaplain residents will provide spiritual consults to patients throughout the Emory hospital system. We will conduct comprehensive assessments in order to examine whether patient (n = 300) outcomes are improved for those receiving chaplain spiritual care augmented by CBCT, in comparison to those receiving spiritual care from chaplains who receive CBCT later in their residency. To this end, study personnel will shadow chaplain residents in both groups and will administer self-report assessments of negative symptomology (depression, anxiety, and loneliness) and well-being (quality of life, hope) to consented patients. In addition, study personnel will audio record chaplain-patient interactions. Patient outcomes will be gathered from retrospective chart reviews and will include use of opioid pain medication, duration of stay, patient’s denial of care, and patients’ Press Ganey satisfaction scores.

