Participants will be approached by a researcher who will explain the study to them and have them sign an informed consent document if they understand the study component and are interested in participating. Chaplain resident participants will receive the CBCT as part of their clinical pastoral education (CPE) curriculum. Chaplain resident participants will receive the CBCT either in the first educational unit (the early-start group) or approximately midway through the residency year (the delayed-start group). Residents in the early-start group will meet virtually for a didactic approximately every two weeks to discuss their residency experience in the context of their CBCT knowledge and caregiving approach. Residents in the delayed-start group will meet for a similarly structured and scheduled didactic on spiritual health topic(s) unrelated to patient care. After the delayed-start group receives CBCT approximately midway through the residency year, the students in the delayed-start group will also meet virtually for the CBCT-focused didactic to discuss their residency experience in the CBCT context and the early-start students will receive the spiritual health didactics on topic(s) unrelated to patient care. All didactics will be 1.5 hours in length. All chaplain resident participants will view the empathic accuracy video and complete the questionnaires at four times during the residency year: before the early-start group receives CBCT (baseline, or T0); after the early-start group completes CBCT (T1); before the delayed-start group receives CBCT (T2), and after the delayed-start group completes CBCT (T3). A subset of the chaplain residents will be interviewed at three time points relative to their training in CBCT. The interviews consist of open-ended questions to further query their learning experiences with CBCT. Researchers will compare differences in the mean scores of empathic accuracy and resiliency measures over time.

[figure not shown]

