To evaluate whether CBCT-informed interventions improve patient outcomes, descriptive statistics (means, standard deviation, standard error) will be used to characterize baseline demographics and responses to self-report assessments. All data will be evaluated for normality, and appropriate procedures will be performed in cases where normality is violated. To evaluate whether CBCT-informed spiritual consults impact patients’ negative symptoms, well-being, and patient health outcomes (duration of stay and patients’ Press Ganey satisfaction scores) we will conduct independent samples t-tests. Dichotomous variables (denial of treatment, opioid use) will be evaluated using chi square tests.

To explore chaplain and patient mediators of the impact of spiritual care consults on patient outcomes, chaplain resident, patient, and chaplain-patient interactions will be tested in mediation analyses using linear regression analysis in order to examine which factors account for improvement in patient outcomes (opioid use, duration of stay, denial of care, patient satisfaction). Any chaplain variables (empathic accuracy or self-reported compassion) that are impacted by CBCT, or patient variables (negative symptoms, well-being) that are impacted by CBCT-informed modules will be entered as independent variables into linear regression analysis with group assignment, and with patient health outcomes as the dependent variable in order to examine whether chaplain, patient, or chaplain-patient interaction variables render group assignment insignificant in accounting for variance in patient health outcomes[^31^](#_ENREF_31).

1. **Compensation:**

No compensation will be provided to participants.

1. **Risks to participation:**

Chaplain residents and Emory Healthcare patients may experience some emotional discomfort while completing the questionnaires. To minimize this risk, all participants will be informed that they are free to skip any questions that are upsetting and that they can stop the questions at any time. In addition, they will be provided help in contacting the Emory Faculty and Staff Assistance Program (FSAP).

In addition, the questionnaires that subjects will fill out as part of this study will contain personal information, and participants may have private pieces of audio recorded.

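### Patient outcomes are to be tested as if 300 patients were independent, although CBCT is given to at most 30 chaplains who each see several of them

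*Protocol*

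**What the plan says.** The Specific Aims section describes a "naturalistic study of up to 30 chaplain residents". Under Procedures in the Design section, CBCT timing is a property of the resident: "Chaplain resident participants will receive the CBCT either in the first educational unit (the early-start group) or approximately midway through the residency year".

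Specific Aim 4 asks "whether patient (n = 300) outcomes are improved for those receiving chaplain spiritual care augmented by CBCT". The comparator is patients visited by residents whose own CBCT course comes at a later stage. A patient's comparison group is therefore set by the training status of the chaplain who visits.

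The Data analysis section then fixes the tests: "we will conduct independent samples t-tests. Dichotomous variables (denial of treatment, opioid use) will be evaluated using chi square tests". The t-tests cover symptoms, well-being, length of stay and satisfaction. The only fallback given for the patient data concerns non-normality. Mixed models appear in the same section, but only for the chaplains' own scores at T0 to T3. The Aim 5 mediation analysis is ordinary linear regression of patient health outcomes on group and candidate mediators, with no term for chaplain.

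**The concern.** A two-sample t-test or a chi-square test on patients takes its error term from variation between patients and assumes that each patient contributes independent information. Here the exposure varies only between chaplains. Any difference between chaplains in skill or style adds to the variance of the group comparison, and the planned tests leave that component out. The t-test would be referred to 300 − 2 = 298 degrees of freedom, when the contrast has about 30 − 2 = 28.

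Three things are at stake.

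- P-values and confidence intervals for the Aim 4 outcomes would be too favourable wherever outcomes vary between chaplains.
- Aim 5 inherits the problem. Patient variables become mediators if CBCT appears to affect them, and mediation is judged by whether the group term loses significance. Both steps rest on the same faulty standard errors. The chaplain-level mediators (empathic accuracy, self-reported compassion) come from at most 30 people but would be treated as 300 independent values.
- The Synopsis says the pilot data will be used to estimate efficacy and to inform a randomized trial. Overstated precision, with no ICC estimated, is a poor basis for sizing that trial.

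**Working it through.** **Inputs from the protocol.** Patients: 300 (Specific Aim 4). Chaplains: at most 30 (Specific Aim 1). Average caseload: 300/30 = 10, the smallest possible average because 30 is a ceiling. The protocol states no alpha, power, standard deviation, ICC or derivation of the 300, so there is no figure of its own to reproduce.

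**Assumptions.** Two-sided alpha 0.05; chaplains split evenly between groups; exposure constant within chaplain; ICC from 0 to 0.20; equal caseloads unless stated otherwise.

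**Formulas.** With m patients per chaplain:

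- design effect DE = 1 + (m − 1) × ICC
- ratio of true to naive standard error = √DE
- effective sample size = 300 / DE
- true type I error of the naive test = 2 × [1 − Φ(1.96 / √DE)]

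**Example, ICC 0.05 and m = 10.** DE = 1 + 9 × 0.05 = 1.45. √DE = 1.204. Effective n = 300 / 1.45 = 206.9. The nominal critical value 1.96 acts as 1.96 / 1.204 = 1.628, which gives a type I error of 0.1036.

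| ICC (assumed) | DE, 30 × 10 | SE ratio | Effective n | Type I error, 30 × 10 | Simulated t-test, 30 × 10 | Type I error, 20 × 15 |
|---|---|---|---|---|---|---|
| 0 | 1.00 | 1.000 | 300 | 0.0500 | 0.0525 | 0.0500 |
| 0.01 | 1.09 | 1.044 | 275 | 0.0605 | 0.0579 | 0.0664 |
| 0.02 | 1.18 | 1.086 | 254 | 0.0712 | 0.072 | 0.0832 |
| 0.05 | 1.45 | 1.204 | 207 | 0.1036 | 0.1017 | 0.1328 |
| 0.10 | 1.90 | 1.378 | 158 | 0.1551 | 0.1564 | 0.2058 |
| 0.20 | 2.80 | 1.673 | 107 | 0.2415 | 0.2418 | 0.3147 |

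The simulations were run under no effect, with 8,000 runs per setting (4,000 for ICC 0.02). They agree with the formula.

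**Chi-square test.** With the ICC on the scale of the observed binary outcome, simulated error is about 7%, 11% and 16% at 0.02, 0.05 and 0.10, much as for the t-test. If the ICC is instead placed on an underlying continuous scale, with an assumed 30% event rate, the error is 0.0812 at 0.05 and 0.1125 at 0.10. The same ICC value means less correlation between the observed binary outcomes on that scale.

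**Uneven caseloads.** With a coefficient of variation of 0.5 in caseload (assumed), DE = 1 + [(1 + 0.5²) × 10 − 1] × ICC = 1 + 11.5 × ICC. This gives 1.575 and an error of 0.1184 at ICC 0.05, and 2.15 and 0.1813 at ICC 0.10. A simulation with more extreme caseloads, from 1 to 30 per chaplain (also assumed), gave 0.083, 0.132 and 0.191 at ICC 0.02, 0.05 and 0.10.

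**Does accounting for the chaplain repair it?** A t-test on chaplain means held simulated error between about 0.044 and 0.053 in every equal-caseload setting, with 30 or 20 chaplains and with continuous or binary outcomes.

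**Precision that is really available.** The detectable difference at 80% power is (1.96 + 0.84) × √(2/150 × DE) standard deviations: 0.32 at ICC 0, 0.34 at 0.01, 0.39 at 0.05 and 0.45 at 0.10.

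**The case against.** The strongest reply has four parts.

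- **Role of the aim.** This is a pilot. The primary outcomes named in the Data analysis section are all measured on chaplains, and Aim 5 is exploratory. No alpha or decision rule is attached to Aim 4. This stands as a limit on the consequences: the primary chaplain analysis is unaffected. It does not make the named tests fit the design.
- **Unknown ICC.** Without a positive ICC there is no inflation, and at 0.01 the error is only about 6%. Outcomes as different as a rating of the visit and duration of stay need not share one ICC. This also stands, so the size is a range and will differ by outcome. But the protocol cannot comfortably assume zero, because Aim 5 proposes that chaplain empathy, compassion and conduct during the visit account for patient outcomes. Nor does the document tie a resident to one campus; a shared site would add to the correlation but is not needed for the argument.
- **Point estimates.** Ignoring clustering does not by itself bias the mean difference or the difference in proportions. That is correct. What carries forward to the later trial is wrong precision and a missing ICC.
- **Left to the SAP.** A separate analysis plan might handle clustering. The protocol, however, does not leave the method open: it names the tests, and they are unsuited to the data it describes.

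**Conclusion.** The concern holds. The protocol prescribes patient-level tests that assume independence for an exposure that varies over at most 30 chaplains, and nothing in it corrects for this. With 30 chaplains and 10 patients each, a nominal 5% test has a true error of about 7%, 10% or 16% at ICC 0.02, 0.05 or 0.10, and true standard errors are 1.09, 1.20 or 1.38 times those reported. This is the favourable case: with 20 chaplains the error is about 13% and 21% at ICC 0.05 and 0.10, and uneven caseloads raise it further. The figures rest on the assumed ICC, a two-sided 5% level, an even split of chaplains and an exposure that is constant within chaplain. The direction needs only a positive ICC. The rule gives wrong error bars as written and must be corrected before the patient data are analysed, even though Aim 4 is not the primary aim.

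**What to change.** In the Data analysis section, replace the patient-level tests with analyses that recognise the chaplain as the cluster:

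- **Continuous outcomes:** a linear mixed model with group as a fixed effect, a random chaplain intercept and small-sample degrees of freedom (Kenward-Roger).
- **Dichotomous outcomes:** a logistic mixed model, or GEE clustered on chaplain with a small-sample correction.
- **Acceptable alternative:** a comparison of chaplain-level means or proportions, which kept the error near 5% in the simulations above.
- **Aim 5:** carry the same clustering into the mediation models and treat empathic accuracy and compassion as chaplain-level variables.
- **Reporting:** give the ICC for each patient outcome, with its uncertainty, for use in planning the randomized trial.

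Each patient record needs the visiting chaplain's study ID. The audio recordings are already to be linked by participant IDs; the questionnaire and chart-review data should carry the same link.

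No extra participants are needed, and SAS Proc Mixed is already named. The costs are wider confidence intervals, as the detectable differences above show, and some restructuring of the Aim 5 regressions. The wider intervals reflect the information the design actually provides.

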During their training program, chaplain residents will provide spiritual consults to patients throughout the Emory hospital system. We will examine whether patient (n = 300) outcomes are improved for those receiving chaplain spiritual care augmented by CBCT, in comparison to those receiving spiritual care from chaplains who receive CBCT at the end of their residency program. To this end, study personnel will shadow chaplain residents in both groups and will administer self-report assessments of negative symptomology (depression, anxiety, and loneliness) and well-being (quality of life, hope) to consented patients. In addition, study personnel will audio record chaplain-patient interactions. Patient outcomes will be gathered from retrospective chart reviews and will include use of opioid pain medication, duration of stay, patient’s denial of care, and patients’ Press Ganey satisfaction scores.

In a final step, using patient chart reviews we will examine chaplain and patient factors that may mediate the link between spiritual consults and improved patient outcomes. Specifically, we will examine whether chaplain empathic accuracy or self-reported compassion mediate the impact of spiritual care consults on patient health outcomes. We will also examine whether patients’ well-being (hope, quality of life), or negative symptoms (depression, anxiety, loneliness) mediate the impact of spiritual care consults on patient health outcomes.

We will also use the ambulatory ambulatory audio recordings of the chaplain-patient interactions to interrogate which aspects of the chaplain-patient interaction mediate improved patient outcomes (see Figure 4). Spiritual consult audio recordings will be coded by 2 trained, independent CBCT instructors for CBCT content. They will also be coded for linguistic and behavioral elements derived from existing models of compassionate interaction in the hospital environment[^9^](#_ENREF_9).

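### Chaplain mediators enter the Aim 5 model only if found to be affected by CBCT in at most 30 residents, so named mediators may go unestimated and those that pass are estimated too high

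*Protocol*

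**What the plan says.** Two places in the protocol describe the chaplain mediators differently.

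- **Design, Procedures** sets no condition: "we will examine whether chaplain empathic accuracy or self-reported compassion mediate the impact of spiritual care consults on patient health outcomes".
- **Data analysis, mediation paragraph** admits only a subset: "Any chaplain variables (empathic accuracy or self-reported compassion) that are impacted by CBCT". Variables that meet this condition "will be entered as independent variables into linear regression analysis with group assignment, and with patient health outcomes as the dependent variable". A parallel condition applies to patient variables. No other route into the model is given.

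The sentence ends by asking whether the entered variables "interaction variables render group assignment insignificant in accounting for variance in patient health outcomes".

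Whether a chaplain variable was affected can be judged only in the chaplain sample. Specific Aim 1 fixes its size: "We will conduct a naturalistic study of up to 30 chaplain residents", in an early-start and a delayed-start group. For Aim 1, the T0-to-T1 change in the early-start group "will be compared to the change in mean score among participants in the delayed-start group over the same time period". The protocol gives no alpha, sidedness, split, effect size or other criterion for deciding that a variable was affected.

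**The concern.** A true mediator must be moved by the intervention. Failing to find that movement in 30 people is weak evidence that it did not happen. Used as an entry rule, the condition makes a stated objective depend on an underpowered earlier result. This has two consequences.

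1. A named mediator that misses the screen is never fitted, so its link to patient outcomes is not estimated, although the Procedures section says it will be examined.
2. A variable that passes has been selected for a large observed CBCT effect, so any indirect effect built on that estimate is too high.

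The Synopsis says that the pilot data will be used to estimate efficacy and to inform a randomized trial. Missing and selectively inflated estimates serve that purpose poorly.

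**Working it through.** The protocol has no power or sample-size figure to reproduce, so the check starts from its sample size and declared assumptions.

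**Inputs.** From the protocol: at most 30 residents in two groups; outcomes analysed as pre-to-post differences; Aim 1 compares T0-to-T1 change between groups. Assumed: 15 per group, two-sided 5% t-test, true shift of 0.5 SD of the change score.

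**Chance of missing a real effect.**
- Noncentrality = d / √(1/n₁ + 1/n₂) = 0.5 / √(2/15) = 0.5 / 0.365 = 1.37.
- Critical t with 28 degrees of freedom = 2.048.
- Noncentral-t power = 26.2%, so the variable is left out 100 − 26.2 = 73.8% of the time. A normal approximation gives 72.3%.

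**Other assumptions, Aim 1 contrast.**

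| Assumption | Left out |
|---|---|
| 0.3 SD, 15:15 | 88% |
| 0.5 SD, 15:15 (base case) | 74% |
| 0.8 SD, 15:15 | 44% |
| 1.0 SD, 15:15 | 25% |
| 0.5 SD, 10:20 | 76% |
| 0.5 SD, 12:12 | 78% |
| 0.5 SD, 15:15, one-sided 5% | 62% |
| 0.5 raw-score SD, pre-post correlation 0.3 to 0.8, change score | 80% to 45% |
| Same, baseline-adjusted | 72% to 40% |

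The two raw-score rows divide 0.5 by √(2(1 − ρ)) for change scores and by √(1 − ρ²) for baseline adjustment. In the base case the effect detectable with 80% power is about 1.06 SD, and 80% power at 0.5 SD would need about 63 per group.

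**Which contrast.** The figures above use the Aim 1 contrast. Data analysis also states "We will examine the effect of CBCT by analyzing the correlated, repeated-measure data (T1 – T0) – (T3 – T2) using mixed linear models". Both groups receive CBCT within those windows, so equal effects cancel, and a screen on that contrast would omit a true mediator about 95% of the time. An uncontrolled pre-post test pooling all 30 residents would omit about 25% at 0.5 SD of the change, but the protocol does not describe such a test.

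**Inflation among variables that pass.** To pass, the observed difference must be at least 2.048 × √(2/15) = 2.048 × 0.365 = 0.75 observed SD, against a true 0.5. In simulation the mean observed difference given a positive pass is 0.94 SD. A mediation simulation used 30 chaplains with 10 patients each, intraclass correlation 0.05, a CBCT shift of 0.5 SD, a link of 0.2 patient SD per chaplain SD, and chaplain-level analysis. The true indirect effect is 0.5 × 0.2 = 0.10. The mean estimate is about 0.10 over all runs and about 0.19 among runs that pass.

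**What removing the screen gains in power.** In the same simulation the 95% interval for the indirect effect excludes zero in about 20% of studies without the screen, and in about 19% when the screen must also be passed.

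**Patient variables.** With 300 patients, the effective number per group is 150 / (1 + 9 × ICC). The miss rate at 0.5 SD is about 1% at ICC 0 and 12% at ICC 0.10. The problem is therefore one of the chaplain variables.

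**The case against.** The strongest objections, and what stands of each:

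- **A variable that CBCT does not move cannot mediate its effect.** This is true of the real effect and stands as a concept. It does not justify treating a low-powered finding as the test of that effect. The CBCT-to-mediator estimate and its interval carry the same information without discarding the variable.
- **The screen costs almost no power.** This stands. A reader might infer that deleting the condition would sharply raise the chance of showing mediation. That would compare detection of the mediator-to-patient link alone with detection of both paths, and mediation needs both. Compared like with like, the gain is about one percentage point.
- **The protocol does not say that an omitted variable is not a mediator.** This also stands. A reader might infer that conclusion, but the text states only which variables are entered. The supportable point is narrower: an omitted variable has no estimate.
- **The significance test is assumed.** Correct. How to judge whether a variable was affected could be settled in the SAP, which is not shown. The nearby wording about group assignment becoming insignificant makes a significance test the natural reading, but it concerns a different step. The entry condition itself is fixed in the protocol.
- **No indirect effect is planned.** Correct. The inflation therefore applies to any such estimate computed later for variables that pass, not to a quantity that the protocol promises.
- **Aim 5 is exploratory, and the condition sits in the same sentence as the rule on insignificance.** Both are true. The first limits the severity. The second means that one rewrite can deal with both, although changing only the later rule would leave the entry condition in place.

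**Conclusion.** The point holds as a matter of complete and unbiased estimation, not of power. Data analysis makes conditional what Procedures states unconditionally, and the condition rests on at most 30 residents. With 15 per group, a two-sided 5% test of the Aim 1 contrast and a true shift of 0.5 SD of the change score, a real chaplain mediator is left out about 74% of the time. The range is roughly 40% to 80% when SD scale, pre-post correlation and sidedness vary. None of these assumptions is a protocol figure. An indirect effect computed only for variables that pass would be nearly doubled in the simulated case. The change is worth making because it is cheap and the pilot is meant to inform a randomized trial, but no decision rule in the protocol depends on Aim 5.

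**What to change.** In the mediation paragraph of Data analysis, delete the entry condition for the mediators already named in Procedures; for consistency, do the same for the patient variables. Fit each named mediator whatever its own CBCT test shows. For each, report the CBCT-to-mediator effect, the mediator-to-outcome effect and the indirect effect, all with 95% confidence intervals. Describe a result as inconclusive unless the interval excludes a relevant effect. Any revision of the rule about group assignment becoming insignificant can be made in the same edit.

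The cost is a wording change and a few more models on data already to be collected. The downside is a larger number of exploratory estimates, with wide intervals for the chaplain mediators. That width reflects what 30 residents can show.
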